#### Outcomes and instruments/scales

##### Primary outcome with a description of the scale

The primary study outcome is the single item “global assessment of inter-sectorial cooperation,” which is part of the Danish questionnaire “*Patients’ attitude to the health care service”* [13] measured 7 months after the enrolment of the patient (additional file 2). This 26-item questionnaire was based on the English questionnaire *“The patient career diary”* [29]. The Danish adaptation was based on interviews with Danish cancer patients and caregivers [30] and the questionnaire template of the English version [29].

Besides our primary outcome, this questionnaire also includes two other single items and five index scales, seeking to address the patient’s attitude towards the cooperation in the health care system. All items have a recall period of 3 months and are answered on a five-point Likert scale from strongly agree (1) to strongly disagree (5). According to the scoring manual, all index scales and items are linearly transformed to values 0 to 100 with higher numbers meaning higher disagreement levels [31].

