#### Sample size

We based our sample size assumptions on knowledge from a Danish intervention study of cancer patients where our primary outcome was used [13]. This study estimated mean values of 56.6 and 69.6 for the control and the intervention group, respectively, and a common standard deviation of 27. Based on these estimates and a clinically relevant difference of 20% between the groups, we calculated a sample size of 194 (2 × 97) participants, with a 0.05 two-sided significance level and a 10% risk of type II error, i.e. a power of 90%. However, as we expect dropout of 30%, our target is to recruit 278 patients.

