#### Plan for data if a participant discontinues

All data will be analysed following the intention-to-treat principles [41], including cases where the GP declines to participate, and no intervention takes place. In case of patient withdrawal of consent, death or relocation, cases will be withdrawal.

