#### Statistical methods

For the between-group comparison of the primary outcome, we will use a standard T-test for the mean difference between two independent means. As a supplementary analysis, we will apply the Mann-Whitney test instead.

Secondary outcomes will be handled similarly, and always according to available manuals. Dichotomous data will be analysed using Fisher’s exact tests and to correct for the multiple comparisons we will apply the Bonferroni correction.

Missing data will be analysed using two strategies - complete-case analysis with only patients with non-missing scores and an imputation approach following the respective manuals. Before imputation, we will investigate if the data are missing randomly or not. Missing data of the EORTC QLQ C-30 and EORTC QLQ INFO-25 will be handled as described in the manual [42].

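### With 30% loss planned and a single-item primary outcome, the stated missing-data rules leave what is in effect a completers-only t-test under an intention-to-treat label

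*Protocol article*

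**What the plan says.** All references are to the protocol article.

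- *Primary outcome with a description of the scale*: "The primary study outcome is the single item" that gives a global rating of cooperation between sectors, measured at 7 months. The scoring manual is cited there only for the conversion to a 0–100 scale.
- *Sample size*: 194 evaluable patients are needed, and "as we expect dropout of 30%, our target is to recruit 278 patients".
- *Plan for data if a participant discontinues*: all data are to be analysed by intention to treat, explicitly including patients whose GP declines and who get no consultation. The next sentence reads "In case of patient withdrawal of consent, death or relocation, cases will be withdrawal".
- *Statistical methods*: the primary comparison is an unadjusted two-sample t-test, with a Mann-Whitney test as a supplement. Missing data are handled by "complete-case analysis with only patients with non-missing scores and an imputation approach following the respective manuals", preceded by a check: "Before imputation, we will investigate if the data are missing randomly or not". A manual is named for missing data only for the two EORTC questionnaires, both of which are secondary.
- *Participant timeline for patient-reported outcomes*: the same scales and items are collected at baseline, 4 months and 7 months.

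**The concern.** An intention-to-treat comparison needs an outcome, or a defensible assumption about the outcome, for every randomised patient. The two stated strategies look like a main analysis and a robustness check. For the primary item they probably amount to the same thing. A scoring-manual rule typically fills a missing item from answered items of the same scale, and a single item has no such companions. A patient who does not return the 7-month form has answered nothing at that visit.

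The discontinuation rule adds to the loss. Relocation need not end follow-up, because follow-up questionnaires go out by email.

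The loss could well be related to the outcome. Patients are having chemotherapy, the questionnaire may take up to an hour, patients know their allocation, and the outcome is their own opinion of how well their care providers cooperate. Randomisation balances the arms as randomised, not the subset who reply. Recruiting 278 instead of 194 restores precision but does nothing about selective loss.

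**Working it through.** **Inputs.** From *Sample size*: "mean values of 56.6 and 69.6 for the control and the intervention group, respectively"; "a common standard deviation of 27"; two-sided alpha 0.05; power 90%; 97 per arm; 30% dropout; target 278. The differences between completers and dropouts used below are assumptions, because the protocol gives none.

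**1. Reproduce the plan's figures.** Per-arm n = 2 × (1.960 + 1.282)² × 27² / δ² ≈ 15,320 / δ². The base of the 20% difference is not stated, so each reading is tried (normal approximation, rounded up):

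| Reading of δ | δ | n per arm |
|---|---|---|
| 20% of 56.6 | 11.32 | 120 |
| 20% of the midpoint 63.1 | 12.62 | 97 |
| Difference of the two cited means | 13.0 | 91 |
| 20% of 69.6 | 13.92 | 80 |

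Only the midpoint reading returns 97 (98 with the exact t distribution). It is back-solved, so the range 11.3 to 13.9 is carried forward. For dropout, 194 / 0.70 = 277.1, hence 278 (139 per arm), which agrees with the protocol.

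**2. Patients planned to be outside the primary comparison.** 0.30 × 278 = 83.4, about 83. The stated power therefore rests on about 194 completers.

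**3. What each strategy does for a missing 7-month form.**
- Complete-case: the patient is left out.
- Manual-based imputation: no other 7-month items exist, so an item-level rule has no input and the patient is again left out.
- Death or relocation: on the natural reading of the discontinuation section, the case is removed before either strategy applies.

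All three routes end in the same t-test on completers.

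**4. Bias of that comparison.** In one arm, let p be the share missing and g the completer mean minus the dropout mean. The mean over all patients is (completer mean) − p × g, so the completer mean is off by p × g. The error in the between-arm difference is p₁g₁ − p₀g₀. With p = 0.30 in both arms this is 0.30 × (g₁ − g₀):

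| g₁ − g₀ (assumed) | Bias, points | Share of 13.92 to 11.32 |
|---|---|---|
| 0 | 0 | 0% |
| 5 | 1.5 | 11% to 13% |
| 10 | 3.0 | 22% to 27% |
| 15 | 4.5 | 32% to 40% |

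Unequal loss can also produce bias when the gap is the same in both arms: with 20% against 40% missing and a gap of 10, the bias is (0.40 − 0.20) × 10 = 2.0 points. Equal loss with an equal gap gives zero.

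**5. Effect on the test.** With 97 per arm, SE = 27 × √(2/97) = 3.88. If there were no true effect, biases of 1.5, 3.0 and 4.5 points would shift the test statistic by 0.39, 0.77 and 1.16. The two-sided false-positive rate would then be about 7%, 12% and 21% instead of 5%.

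**The case against.** - **The manual is not shown.** A reader might infer that manual-based imputation certainly cannot fill the item. The documents do not prove that. What stands is that the protocol describes no other imputation for this item, and that an item-level rule has nothing to work from when the form is not returned.
- **Intention to treat is partly honoured.** It would be wrong to call the claim empty. The protocol keeps patients whose GP declines, which is the main adherence threat here. The label fails for missing outcomes and removed cases only.
- **The discontinuation sentence is garbled.** It could mean that the patient is recorded as withdrawn from follow-up. Under a heading about data after discontinuation, exclusion is the more natural reading. Either way the sentence needs rewording.
- **Deaths may be few.** Eligibility requires expected survival beyond 7 months, and a patient who has died has no 7-month opinion. Leaving out that score is not in itself an error; not saying how death enters the comparison leaves its meaning open.
- **The missingness check has some use.** It can show departure from missing completely at random and identify predictors of loss, which can inform an imputation model. It cannot rule out loss that depends on the unseen scores, and no alternative analysis is tied to its result.
- **An article may leave detail to an analysis plan.** So the absence of a mixed model or a sensitivity analysis is not by itself a fault. The point rests on what the article does state: an intention-to-treat claim beside two strategies that do not deliver it for the primary item.
- **The 30% is a planning allowance.** Two email reminders and a postal one may reduce the loss. The trial is nevertheless sized on it.

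**Conclusion.** The point holds as an inconsistency between the intention-to-treat claim and the stated handling of missing data. For the primary item, the plan as written gives in effect a completers-only t-test, with about 83 of 278 randomised patients expected to be outside it. The second strategy would not test how far the result depends on them.

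This rests on two readings: that the manual's rules work at item level, and that the discontinuation sentence means exclusion. Both are likely, but the documents do not settle either.

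A reader might go further and infer that the result will be biased, or biased by a stated fraction of the planned effect. The documents do not support that. The bias depends on differences between arms that are unknown: it is 0 to 4.5 points under assumed differences of 0 to 15, and zero if loss and gap are equal in both arms. The yardstick of 11.3 to 13.9 points is itself uncertain, because the base of the 20% is not given.

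**What to change.** **Primary item.** Use multiple imputation by arm, or a longitudinal model with baseline as a response, based on the baseline, 4-month and 7-month scores already collected. Include all randomised patients, including those with a baseline score only. A model limited to patients with some follow-up would still leave out those who return no form.

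**Sensitivity.** Add a delta-adjusted analysis in which the imputed scores are shifted, separately by arm, over a stated range. Describe the missingness check as a search for predictors of loss, not as a test of whether loss is random.

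**Scoring manuals.** Keep their rules for missing items within multi-item scales.

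**Discontinuation section.**
- Drop relocation as a reason for removal and keep sending the emailed questionnaire.
- Retain data collected before death, report deaths by arm, and state how death enters the estimand. Both a longitudinal model and imputation otherwise extrapolate scores beyond death without saying so.
- Keep data collected before withdrawal unless consent to use them is withdrawn.

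**Cost.** A few more analyses, an explicit assumption about deaths, and continued emailing of a few relocated patients. No new instrument or visit is needed.

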### Methods: monitoring

#### Monitoring

During the trial, there will be no monitoring of data by researchers or its sponsors, except when sending out reminders. No interim analysis is planned.

#### Harms and description of auditing if any

No harm to patients or other study participants is expected. Unexpected harmful, uncomfortable or abrasive experiences can be communicated verbally or in writing to the project group as stated in the information material given at study inclusion.

### Methods: patient and public involvement

The project idea was conceived in a working group called “Doctors’ Partnership” at the Lillebaelt Hospital, Vejle, Denmark. Representatives from the Patient and Relatives Council at the Hospital participated in the working group. Furthermore, the council have proofread the information material and questionnaires for the study. In the pilot study, the burden of the intervention and questionnaires was assessed by patients and were found acceptable. There are no plans to involve patients in recruitment and conduct of the study, besides in the development phase and interpretation of the results.

We are planning to host a workshop with the Patient and Relatives Council to discuss the results from the study and its implications for cancer patients. Final results will be available for patients and the public at the project website, as stated in the information material.

### Ethics and dissemination

#### Permissions and registrations

The Regional Ethics Committee on Biomedical Research in Denmark (S-20142000-138) and the Danish Data Protection Agency (2014-41-3534) have approved the study. Collection of data will be handled according to national law restrictions. The study is indexed at https://www.clinicaltrials.gov (NCT02716168), registered 03 March 2016.

#### Plan for communication important protocol modifications

Modification to the protocol will be announced in Danish at the project website http://www.sdu.dk/psp and in English at https://www.clinicaltrials.gov.

#### Who will obtain informed consent?

The outpatient clinic nurses at the Oncological Department will obtain informed consent from patients. The consents forms are stored at the Department of Oncology, clinical research unit.

The project nurse responsible for GP participation will obtain oral consent from GPs in the intervention group.

GPs in the control group will be informed about the study at the four-month questionnaire but are not requested to return a consent form.

#### Confidentiality

Assessment and information about potential participants are kept in the hospitals electronic patient record. At the eligibility assessment before inclusion, only the physician responsible for the treatment and the nurse manager at the department has access to the electronic patient record. After informed consent from the patient, the project manager ([name]) has access to the electronic patient record.

#### Access to data

Data access is restricted to the research group including the statistician.

The project nurses do not have access to obtain data from the project database in RedCap® [40]. They can only view data in connection with enrolment and view data necessary for project management. All spreadsheets in RedCap® [40] are logged. At the end of the analytical phase of the study, all electronic data will be transferred to the Danish National Archives.

#### Provisions

GPs in the interventions group will receive a fee for the video consultations, which will be 48 or 97 Euros for up to 30 min and above 30 min, respectively. GPs will receive 18 euros for filling in a questionnaire at 4 months.

Patients and oncologist will not receive any reimbursement.

#### Dissemination policy

Trial results will be published in peer-reviewed journals, discussed at national and international conferences and communicated for the public at the project website http://www.sdu.dk/psp.

#### Ethical considerations about the trial

Data security when conducting video-consultation is essential. Patients show a high degree of trust in regards to data security because they trust the healthcare staff using the technology. Therefore, a high level of data security is needed, and all video-consultations are held on the Region of Southern Denmark secure videoconference servers with the use of virtual meeting rooms. The servers offer a highly secure connecting with no third party data processing. The meeting room can only be access by the participating parties.

Before the video-consultation patient might have spoken about confidential matters, which they have not discussed with all healthcare providers, e.g. alcohol consumption or smoking, this could place the patient in a dilemma. Therefore, the intervention-guide for oncologist and GPs include a note about this.

## Discussion

Video-based consultation that brings the cancer patient, the GP and the oncologist together in the early phase of treatment may facilitate a sense of partnership that is powerful enough to improve the patient’s perception of intersectoral cooperation, continuity of cancer care and health-related quality of life. Beyond the RCT design, we intend to examine the consultations qualitative with a focus on the structure, content and benefits from this shared consultation. The method and description of this analysis are beyond the scope of this paper.

Based on our pilot study we believe that the study is feasible and intent to test the intervention in a pragmatic randomised controlled trial.

### Study limitations

A possible limitation of the study is the IIRS and CCCQ questionnaires. They were translated from English to Danish for this study. Although the translation was based on the guidelines for the process of cross-cultural adaptation of self-report measures proposed by Beaton et al. [39] they have not been validated in a Danish setting before study start. However, all other outcome measures have been validated and used before in a Danish mixed cancer-setting.

GPs can have patients in both groups leading to the possibility of a spillover effect. However, we anticipated this to be of minor significance since there are more than 500 GPs in the Region where recruitment is planned and the mean number of incident cancer patients per year per GP is eight. Therefore, most of the participating GPs would only have one patient enrolled in the study. Finally, the use of video-consultations is relatively new to most GPs in Denmark especially in regards to patient communication. Therefore, logistical concerns and technological barriers could be a limitation of the study.

## Data Availability

Not applicable.

## Abbreviations

CCCQ: Cancer Care Coordination Questionnaire
DSM-IV: Diagnostic and Statistical Manual of Mental Disorders, Fifth Edition
EORCT – QLQ C 30: European Organization for Research and Treatment Quality of Life Questionnaire C-30
EORCT INFO 25: European Organization for Research and Treatment Information Questionnaire 25
GAD-7: The Generalised Anxiety Disorder seven scale
GP: General practitioner
IIRS: Illness Intrusiveness Rating Scale
OPEN: Odense Patient Data Explorative Network, Department of Clinical Research, University of Southern Denmark and Odense University Hospital
PHQ-9: The Patient Health Questionnaire nine scale
RCT: Randomised controlled trial
SPIRIT-PRO: Standard Protocol Items: Recommendations for Interventional Trials – Patient-Reported Outcomes
